### Study aims

The Study of Novel Approaches to Weight Gain Prevention (SNAP) is a two site, randomized clinical trial funded by the National Heart Lung and Blood Institute. The two clinical sites are at The Miriam Hospital ([name], PI) and The University of North Carolina at Chapel Hill ([name], PI). The Coordinating Center is at Wake Forest School of Medicine ([name], PI). SNAP is comparing the efficacy of self-regulation plus small behavior changes intervention, a self-regulation plus large behavior changes intervention, and a minimal treatment control condition in preventing weight gain in 600 young adults age 18 – 35 over an average planned follow-up of 3 years.

The primary hypothesis is that the magnitude of weight gain across 3 years will differ among the three groups. Specific *a priori* hypotheses are that the magnitude of weight gain across the 3 years will be lowest in the self-regulation plus large behavior changes intervention, followed by the self-regulation plus small behavior changes intervention, and greatest in the control condition.

Secondary aims compare the 3 conditions on mean weight gain at 2 years, on the proportion who gain <1 pound or >1 pound at 3 years, and on the proportion who become obese at 3 years. The three groups are also compared on changes in behavior (e.g. diet, physical activity, disordered eating behaviors, use of healthy and unhealthy weight control practices), psychosocial measures (restraint, depression), and changes in CVD risk factors (including blood pressure, lipids, insulin sensitivity, and waist circumference). The study will also examine demographic and psychological variables that may predict weight change over the average follow-up of 3 years and/or moderate the effects of the interventions, including initial BMI, ethnicity, age, scores on the Eating Inventory, and treatment preference and examine potential mediators of the effect of the interventions, including changes in diet, physical activity, restraint, self efficacy and frequency of self-weighing.

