### Outcome measures

Assessments are completed at baseline, month 4, year 1, and year 2. Depending on when participants entered the trial, they may also complete a year 3 and year 4 assessment. All assessments are completed by staff members who are masked to the participants’ intervention assignment and have been certified by the Data Coordinating Center in the appropriate conduct of the measures. Specific protocols for the conduct of these measures are available from the Action for Health in Diabetes (Look AHEAD) trial [28]. Participants are provided a $50 honorarium for each assessment visit (with the exception of the baseline visit). Table 5 shows the schedule of assessments included in this trial.

**Table 5 T5:** Data collection schedule for SNAP

**Measure**	**Month**					
	0	4	12	24	36	48
Anthropomorphic						
Weight (primary outcome)	X	X	X	X	X	X
Height	X	X	X	X	X	X
Waist circumference	X	X	X	X	X	X
Body composition with impedance	X	X	X	X	X	X
Body composition with BodPod (UNC only)	X	X	X	X	X	X
Behavioral and cognitive						
Diet (Food Frequency Questionnaire)	X	X		X		
Specific questions about diet	X	X	X	X	X	X
Physical activity: Paffenbarger	X	X	X	X	X	X
Sedentary activity	X	X	X	X	X	X
Objective (arm bands)	X	X	X	X		
Weight history	X					
Weight management strategies	X	X	X	X	X	X
Self-weighing	X	X	X	X	X	X
Eating disorders assessment	X	X	X	X	X	X
Eating inventory	X	X	X	X	X	X
Autonomous motivation	X	X	X	X	X	X
Smoking, alcohol use	X	X	X	X	X	X
Sleep habits	X	X	X	X	X	X
Neighborhood, environment	X	X	X	X	X	X
Medical						
Blood pressure	X	X	X	X	X	X
Fasting lipids, glucose, insulin	X			X		
Medication use	X	X	X	X	X	X
Medical events		X	X	X	X	X
DNA, serum, plasma	X			X		
Psychological assessments						
Depression (CES-D)	X	X	X	X	X	X
Life events	X	X	X	X	X	X
Perceived stress	X	X	X	X	X	X
Quality of life	X	X	X	X	X	X
Other questionnaires						
Demographic data	X	X	X	X	X	X
Contact information	X	X	X	X	X	X
Weight status of friends and family	X	X	X	X	X	X
Treatment preference, satisfaction and post-treatment feedback	X	X	X	X	X	X
Adherence (Intervention groups only)						
Attendance at adherence sessions		Throughout				
Monthly submission of weight data		Throughout				

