#### Behavioral measures

**Diet** Dietary intake is assessed at baseline, month 4 and month 24 with the Block Food Frequency, a semi-quantitiative food frequency questionnaire that has been used in a number of weight loss intervention trials including Look AHEAD, DPP, and PRIDE [29]. For each food item on the Food Frequency, participants report the frequency of consumption and the portion sizes consumed over the past month. An important reason for selecting this approach to dietary assessment is that the participants can complete the FFQ on-line at their own convenience. The FFQ is supplemented with specific questions related to frequency of meals at fast food restaurants, frequency of meals at other types of restaurants, and consumption of sweetened beverages.

**Physical activity** The Paffenbarger Activity Questionnaire (PAQ) [30] is administered as a measure of physical activity by trained interviewer at each assessment visit. The PAQ has been used to assess leisure time activity in many weight loss trials and can be scored to provide an estimate of calories expended per week in overall leisure time activity and in activities of light (5 kcal/min), medium (7.5 kcal/min), and high (10 kcal/min) intensity.

Given the increasing recognition of the importance of sedentary activity, independent of physical activity, sedentary activity is assessed at each assessment visit using a self-report questionnaire, which asks respondents to indicate the number of hours they spend on a typical weekday and a typical weekend day doing a variety of sedentary activities [31].

The SenseWear Pro Armbands (Body Media, Pittsburgh PA) provides an objective assessment of physical activity at baseline, month 4 and month 24 in order to confirm the self-report data and to determine whether participants in the small and large changes conditions have different patterns of activity that reflect the different exercise recommendations given to the two groups [32]. Participants are instructed to wear the device during all waking hours (except swimming and showering) for a full week; monitoring for at least 10 hours per day for at least 4 days in the week (including at least one weekday and one weekend day) is considered adequate for analysis.

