The secondary aims will be examined as follows. Pairwise differences in the secondary outcome measure, weight gain of greater than 1 pound from baseline (yes/no), will be assessed using generalized estimating equation (GEE) methods. Pairwise differences in mean weight changes from baseline to 24 months post-randomization among intervention arms will be assessed with linear contrasts and Wald tests within the framework of the general linear models used for the primary aim. Two-sided tests will be used with Bonferroni-adjustment to maintain overall Type I error for this secondary aim at 0.05. Generalized linear models will be used to compare the changes in behaviors and risk factors over time among the three treatments in a manner similar to that used for assessing weight changes. The effects of demographic and psychological measures on the outcomes will be examined by including initial BMI, ethnicity, age, scores on the eating inventory, and intervention preference. Significant interaction effects will be plotted to illustrate the moderating effects, further assisting the interpretation for whom and under what circumstances the intervention has different effects. To examine potential mediators of the effect of intervention, i.e., whether or not there is evidence that changes in diet, physical activity, restraint, and self-regulatory behaviors may be in the causal pathway between the intervention and weight gain, a series of three linear regression models will be fitted to test for mediators following the procedures introduced by Baron and Kenny [43]. The Sobel’s test will be used to test the significance of the indirect effect. The joint effects of multiple mediators will also be tested [44]. For the secondary outcome of weight gain (yes/no), logistic regression models will be fitted to assess meditational effects [45].

We pre-specify three planned subgroup comparisons. We will assess, using tests of interaction, whether the relative efficacy of the intervention varies according to baseline BMI (<25 kg/m^2^ versus ≥25 kg/m^2^), age (<25 years versus ≥25 years), and gender.

The fidelity of intervention delivery within the two clinical sites will be assessed by comparing measures of adherence and weight control. Adverse events will be tallied by intervention assignment and for important clinical subgroups. We will report event rates per person years and use Poisson regression to compare rates of any commonly occurring events among intervention groups.

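### The planned Sobel test of mediation is conservative and gives up roughly 10 to 20 points of power for modest paths; the mediator list and armband schedule also need reconciling

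*Protocol article*

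**What the plan says.** All places are in the protocol article.

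- **Method (Analysis plan).** For mediation, "a series of three linear regression models will be fitted to test for mediators following the procedures introduced by Baron and Kenny". Sobel's "test will be used to test the significance of the indirect effect". In addition, "The joint effects of multiple mediators will also be tested", by a cited method, and logistic models are planned for the yes/no weight-gain outcome. No significance level, path sizes or power are given for mediation.
- **Mediators in the Study aims.** The list is given as "including changes in diet, physical activity, restraint, self efficacy and frequency of self-weighing".
- **Mediators in the Analysis plan.** The question there is whether "changes in diet, physical activity, restraint, and self-regulatory behaviors may be in the causal pathway". Self efficacy is not in this list.
- **Armband (Behavioral measures).** The device "provides an objective assessment of physical activity at baseline, month 4 and month 24".
- **Armband (Outcome measures, Table 5).** The row beginning "Objective (arm bands" carries four marks, under months 0, 4, 12 and 24.

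**The concern.** An indirect effect is the product of two coefficients: *a*, the effect of arm on the mediator, and *b*, the effect of the mediator on weight change given arm. Sobel's test divides the estimated product by a first-order standard error and refers the ratio to a normal distribution. When neither path is many standard errors from zero, the product is skewed and the ratio is too small too often. The test then rejects less often than its nominal level allows, both under the null and when mediation is real. The aim is to learn how the interventions work, so a true mediator could be reported as unsupported for a reason that a better interval would remove.

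The other two items are inconsistencies. A mediator that is named but has no listed measure cannot be analysed from what the article describes. A month-12 armband assessment that appears in only one of two places may or may not be carried out.

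**Working it through.** **Inputs from the article.** There are 200 per arm. Anticipated loss is 7.5% at month 4, a further 7.5% at month 12 and 5% per year thereafter, so 7.5 + 7.5 + 5 = 20% by month 24. That leaves 160 per arm, or n = 320 in a pairwise comparison.

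**Assumptions.** Arm is coded 0/1, residual SDs are 1, and tests are two-sided at 0.05 because no level is stated for mediation. Path sizes *a* and *b* are assumed. There is no stated mediation figure to reproduce.

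**Why Sobel is conservative, in one case.**

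- SE(*a*) = √(1/(320 × 0.25)) = √(1/80) = 0.112
- SE(*b*) = 1/√320 = 0.056
- With *a* = 0.30 and *b* = 0.15: z_a = 0.30/0.112 = 2.68 and z_b = 0.15/0.056 = 2.68
- Sobel z = z_a·z_b / √(z_a² + z_b²) = 2.68/√2 = 1.90

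If both estimates landed exactly on these true values, each path would be clearly significant, yet Sobel's statistic would fall short of 1.96.

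**Simulated power at n = 320** (2,000 to 3,000 replicates per run; a range reflects separate runs or a differing direct effect):

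| *a*, *b* | Sobel | Product (Monte Carlo) interval | Loss, points |
|---|---|---|---|
| 0.28, 0.14 | 27% | 47% | 20 |
| 0.30, 0.15 | 34% | 56% | 22 |
| 0.30, 0.20 | 54% | 70% | 16 |
| 0.40, 0.20 | 78–79% | 88–90% | about 10 |
| 0.28, 0.39 | 67% | 70–71% | 3 to 4 |
| 0.52, 0.26 | 98% | 99% | 1 |
| 0.78, 0.39 | 100% | 100% | 0 |

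The rows with *a* of 0.28, 0.52 and 0.78 were run with arm coded −1/+1 at 0.14, 0.26 and 0.39. The between-arm difference is twice that value.

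**Type I error at n = 320.** With *a* = 0.30 and *b* = 0, Sobel rejects 0.7% to 1.0% of the time and the interval about 3.5%. With *a* = 0 and *b* = 0.39, the figures are 4.2% and 5.4%. The simulation error there is √(0.05 × 0.95/3000) = 0.4 points, so the second is compatible with 5%.

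**Are modest paths plausible here?** The Sample size calculation targets 1.36 kg with at least 90% power but gives no SD. Solving SD = 1.36 / ((z₁₋α/₂ + z₀.₉₀)·√(2/n)) gives 4.20 kg (200 per arm, α 0.05) down to 3.20 kg (150 per arm, α 0.0167). The target is therefore 1.36/4.20 = 0.32 to 1.36/3.20 = 0.43 SD. Shared equally among the five mediators in the Study aims, which is only an illustration, that is about 0.065 to 0.085 SD each. The cases (0.30, 0.15), (0.30, 0.20) and (0.40, 0.20) have products of 0.045, 0.06 and 0.08, so they lie in or near that region.

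**Self efficacy.** Of the five mediators in the Study aims, four have a measure: the food frequency questionnaire, the Paffenbarger questionnaire and armband, the Eating Inventory restraint scale, and the self-weighing question. Self efficacy has no row in Table 5 and no description in the measures sections. The nearest instrument, the Treatment Self Regulation Questionnaire, is described as measuring autonomous and controlled motivation.

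**Armband.** The text gives three time points and Table 5 gives four. They agree on months 0, 4 and 24 and differ at month 12.

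**The case against.** **The power figures rest on chosen effects.** This stands. The article states no path sizes, and at (0.30, 0.15) the better interval itself reaches only 56%, so much of that shortfall comes from the assumed effects. A reader might infer that the mediation aim is badly underpowered. The documents do not support that: Sobel reaches 78% or more at (0.40, 0.20) and loses almost nothing for large paths. Only the relative loss for modest paths is shown.

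**A significant total effect may be taken as a strict precondition.** A reader could infer this from the Baron and Kenny name and conclude that power collapses. The Analysis plan does not say that Sobel's test depends on that step. The size of any penalty also depends on the total effect assumed. The trial is sized for about 1.36/3.75 = 0.36 to 1.36/3.31 = 0.41 SD at 160 per arm (α 0.05 and 0.0167). With a total effect of about 0.38, adding the step lowers power at (0.40, 0.20) from 78–79% to about 73%. Much larger penalties need a total effect well below the design value.

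**The method is valid and the aim is secondary.** This also stands. There is no inflation of false positives, and a joint test of several mediators is planned by a method not visible here. The reason to change is a gain in power at almost no cost.

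**An article may condense its list of instruments.** That is fair in general, but Table 5 is presented as the data collection schedule and goes down to sleep habits and neighborhood. The Analysis plan's own list also drops self efficacy. The armband conflict matters little for mediation, because the Paffenbarger questionnaire is given at every visit.

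**Conclusion.** The point holds as a matter of efficiency. Sobel's test is conservative. At about 160 per arm it loses roughly 10 to 20 points of power against a product-distribution interval for modest paths, a few points when one path is strong, and one point or less when both are large. Neither method inflates type I error beyond simulation error. The size rests on assumed standardised paths, a 0.05 level and the article's anticipated loss to month 24. The self-efficacy and armband mismatches are confirmed from the text and are minor. The primary comparison, the sample size and the other secondary comparisons of the arms are not touched.

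**What to change.** 1. In the Analysis plan, replace Sobel's test with a bootstrap or product-distribution (Monte Carlo) confidence interval for the indirect effect, and state that a significant total effect is not required first.
2. Either name the self-efficacy instrument and its time points in Table 5 and the measures text and add it to the analysis list, or remove it from the Study aims.
3. Make Table 5 and the Behavioral measures text agree on whether the armband is worn at month 12.

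Item 1 costs a sentence and slight extra computing. Items 2 and 3 are wording if they only record what is already being done. None of the three needs more participants.

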### Self-guided behavior changes (Control condition)

Participants in the self-guided condition receive one face-to-face group session in which information about behaviors associated with weight gain in young adults and the health consequences of weight gain are presented. Self-weighing is introduced as a preventive strategy, both the small changes and large changes approaches are described, and 2–3 internet resources consistent with each approach are provided. In addition, participants receive an overview of the principles of both the Large and Small Changes approaches and are encouraged to select whichever approach they feel will work best for them and use it to prevent weight gain over the course of the study. Participants have access to a study website where quarterly newsletters are posted with information about weight gain prevention and healthy eating and physical activity strategies, as well as links to the internet resources mentioned above, but no active assistance is provided in implementing these approaches.

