#### Self-regulation

The goal of both interventions is to prevent weight gain through the self-regulation of eating and exercise behaviors, a model that was used successfully in STOP Regain [15]. Participants are given scales for home use and are taught core self-regulation skills, including: a) to weigh themselves daily; b) to detect small changes in weight as soon as they occur; c) to implement problem solving and behavioral strategies to deal with these changes; d) to evaluate the success of these strategies; and e) to provide self-reinforcement for successful weight maintenance or to make changes in their behavior if gains occur. To help participants detect small changes in their weight and to guide appropriate actions, they are taught to use a red, yellow, and green weight monitoring system. Based on their preference, participants use either a web-based or Short Message Service (SMS) to report their weight at least monthly; based on their reported weight, they receive immediate automated feedback as to their color zone for the week (see color zone descriptions below) and are instructed to practice either reinforcing their own success or taking the corrective appropriate action. Participants also receive monthly email tip sheets corresponding to their color zone from a study interventionist. The color zones for both interventions are identical. For participants who lost weight during the initial 8 week intervention, the green zone (Go!) is established based on their new weight allowing a minimal amount of regain. For participants ending the initial 8 week intervention at or above their starting weight, the green zone is established as less than 1 lb below their starting weight. These participants are encouraged via email to reinforce themselves for their success and receive small “green” tokens via postal mail from the study staff (e.g. green tea, dollar bill) on a preset intermittent schedule of approximately once per month to teach the benefits of reinforcement. A participant is considered to be in the “yellow zone (Caution!) if his/her current weight is above their green zone weight but at or below their starting weight. These participants are encouraged to return to self-monitoring of diet and activity (consistent with their treatment condition), to identify behavior changes that may be causing the weight gain, and to use problem solving and behavior change strategies to reverse these changes. Finally, a participant is considered to be in the “red zone” (Stop!) if his/her current weight is above their starting weight. If this occurs, behavior changes consistent with the participant’s treatment condition are prescribed. These participants are also offered up to two 20-minute individual sessions with an interventionist, either in-person or via phone or email, that focus on motivation, problem solving, and a review of techniques consistent with the participant’s treatment condition. A tip sheet encouraging behavior change is emailed to all participants in the yellow or red zones on a monthly basis with quarterly phone calls to those who have not submitted their weight or are in the red zone.

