#### Anthropometric and clinical measures

At each assessment visit, weight is measured in light clothes without shoes, on a calibrated scale, and height is determined using a wall mounted stadiometer. Two measures of each are completed and the average of the two is used. The weight and height measures are used to calculate Body Mass Index (weight in kilograms divided by height in meters squared). Waist circumference is measured at the midpoint between highest point of iliac crest and lowest point of costal margin using a Gulik tape measure; two measures of waist circumference are taken; if the difference exceeds 1.0 cm, a third measure is taken. Both sites complete measures of body composition with the RJL Systems Quantum II impedance machine. In addition, participants at UNC also have body composition assessed with the BodPod (COSMED USA, Inc.) Participants are asked to fast for 4 hours and to refrain from strenuous exercise for 8 hours prior to these body composition measures. Blood pressure is assessed with a Dinamap Monitor Pro 100. Cuff size is determined by arm circumference. Three readings are taken, with a 30-second wait between. At baseline and month 24 only, fasting blood samples are taken for analysis of lipids (total cholesterol, HDL-C, LDL-C and triglycerides) and glucose and insulin levels; DNA is collected for future genetic analyses in those who consent to this component. At each assessment, participants are asked to report all prescription and non-prescription medications and to indicate any health problems that they have experienced since the last assessment.

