### Safety, and monitoring of serious adverse events and other medical events

Data are collected at in-person visits and if contacted by a participant between visits regarding any medical issues that might affect safety of the intervention or outcomes (e.g. pregnancy). Serious adverse events are defined as hospitalizations, fatal or life-threatening events, events resulting in significant or persistent disabilities, birth defects or congenital abnormalities, or important medical events that investigators judge to represent significant hazards or harm to research subjects. Other medical events and alert values for assessments of clinical relevance are also monitored and reported to participants. Standard guidelines are used to determine alert values and recommend medical follow-up to participants for blood pressure, lipid and glucose levels. If a participant has a greater than 20% weight loss from baseline, reaches a BMI ≤ 18.5 kg/m^2^ or loses more than 15 pounds in a month, the participant is seen and counseled. If further weight loss occurs, intervention activities are suspended. If a participant develops an eating disorder, the participant is referred to care, and intervention is discontinued and not resumed until cleared by their care provider. Intervention activities are also stopped during pregnancy or if there are injuries or illnesses where weight loss and/or physical activity would be contra-indicated. Intervention is resumed 6-months post-partum or when injuries or illnesses resolve.

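### Adverse event rates are compared across arms without limiting the source of reports, so extra staff contact may inflate the active-arm rates relative to control

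*Protocol article*

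**What the plan says.** **Analysis.** The Analysis plan section tallies adverse events by arm. It then states "We will report event rates per person years" and that the team will "use Poisson regression to compare rates of any commonly occurring events among intervention groups". Neither statement restricts the events by how they came to light.

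**How events enter.** The safety monitoring section says "Data are collected at in-person visits and if contacted by a participant between visits regarding any medical issues". It does not say whether intervention sessions count as in-person visits.

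**Contact by arm.**
- Control: "Participants in the self-guided condition receive one face-to-face group session", plus a website with newsletters.
- Each active arm (Intervention contact, Table 2, Self-regulation): 8 weekly and 2 monthly group sessions, two 4-week refreshers a year from year 2, up to two individual sessions for participants in the red zone, and "quarterly phone calls to those who have not submitted their weight or are in the red zone".
- The section on common components of the active interventions gives both active arms the same contact frequency.

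**Common assessments.** At each assessment every participant is asked "to indicate any health problems that they have experienced since the last assessment" (Anthropometric and clinical measures). Table 5 has a row "Medical events", marked at months 4, 12, 24, 36 and 48 with no restriction by arm. The assessments are "completed by staff members who are masked" to assignment (Outcome measures).

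**The concern.** If the chance that an event is recorded depends on how often a participant meets or writes to staff, and that frequency is set by randomization, the recorded rate mixes true incidence with opportunity to report. Here the opportunity is clearly unequal between either active arm and control. Session leaders also know which arm they are treating; only assessment staff are described as masked. In addition, the safety section pauses intervention activities for pregnancy, injury or illness, which gives active participants a practical reason to tell staff between visits that controls largely lack.

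The active-versus-control safety contrast is at stake. The Large Changes arm prescribes calorie restriction and 250 minutes of activity a week to adults with a BMI from 21, so readers will look at that contrast. As the analysis is written, an excess of common events in an active arm could not be separated from fuller reporting.

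**Working it through.** The article states no event rate, count, dispersion or safety power, so there is no figure of its own to reproduce. Every capture share, event mean and dispersion below is an assumption.

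**1. Opportunity to report**
- Scheduled follow-up (Study design): 2 + 0.8 + 0.2 = 3.0 years, matching the stated average.
- Post-baseline assessments per person, all arms: 3 + 0.8 + 0.2 = 4.0. With the losses in the Sample size calculation section: 0.925 + 0.85 + 0.80 + 0.8 × 0.75 + 0.2 × 0.70 = 3.3.
- First four months, counting every session and the shared month-4 assessment: 10 + 1 = 11 occasions in an active arm and 1 + 1 = 2 in control. This holds only if group sessions count as in-person visits, which the text leaves open.
- Gaps between assessments: 4 months, then 8, then 12.

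**2. Bias from unequal capture when the true rate ratio is 1**

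Let *s* be the share of events caught by the common assessments, and *ea* and *ec* the shares of the remainder caught through other contact in an active arm and in control. Then

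observed rate ratio = [s + (1 − s)·ea] / [s + (1 − s)·ec]

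| s | ea 0.25, ec 0.05 | ea 0.5, ec 0.1 | ea 0.5, ec 0 |
|---|---|---|---|
| 1.0 | 1.00 | 1.00 | 1.00 |
| 0.9 | 1.02 | 1.04 | 1.06 |
| 0.8 | 0.85/0.81 = 1.05 | 0.90/0.82 = 1.10 | 0.90/0.80 = 1.13 |
| 0.5 | 0.625/0.525 = 1.19 | 0.75/0.55 = 1.36 | 0.75/0.50 = 1.50 |

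Using only events elicited at the common assessments reduces the expression to s/s = 1.00, provided recall at the assessments is the same in each arm. For Small versus Large Changes, equal contact frequency gives no reason for *ea* to differ between the arms, so the ratio stays at 1.

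**3. Variance (secondary)**

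For negative binomial counts with mean μ per person and dispersion k, the variance is φ = 1 + μk times the Poisson variance. The Poisson standard error is too small by √φ, and the true two-sided error of a nominal 5% test is 2·[1 − Φ(1.96/√φ)].

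| μ | k | √φ | True error |
|---|---|---|---|
| any | 0 | 1.00 | 0.050 |
| 0.1 | 1 | 1.05 | 0.062 |
| 0.3 | 1 | 1.14 | 0.086 |
| 1 | 1 | 1.41 | 0.166 |
| 2 | 1 | 1.73 | 0.258 |

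In simulation (1,500 trials per setting, 200 per arm, equal capture, k = 1), replacing the Poisson by a robust standard error moved the rejection rate from 0.087 to 0.059 at μ = 0.3, from 0.168 to 0.053 at μ = 1, and from 0.265 to 0.049 at μ = 2.

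**4. The two issues are separate**

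With s = 0.8, ea = 0.5, ec = 0.1, μ = 1 and k = 0, the simulated rate ratio was 1.10. The rejection rate was 0.130 with Poisson errors and 0.135 with robust errors. A better variance does not remove capture bias.

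**The case against.** The strongest reply is that the design already contains the safeguard. Masked staff ask all arms about problems since the previous assessment, on the same schedule. An event mentioned at a session is asked about again at the next assessment, just as it is for a control participant. Extra contact then adds only events that would have been forgotten, or lost because the participant dropped out. This stands: it bounds the bias, and complete recall would make it zero. It does not settle the matter, because gaps of 8 and 12 months make it plausible that minor common events are forgotten, and because the analysis is not confined to those assessments.

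Some of the contacts also fit the stated capture rule poorly. The between-visit route is contact made by the participant, whereas the quarterly calls are made by staff and only to some participants. Refreshers may be online or by email. That also stands, and it is why the initial sessions are the clearest source of imbalance.

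A reader might infer something stronger: that the comparison is biased against the active arms and that its intervals are too narrow. The documents support neither as fact. The size of any bias is unknown and may be nil. The article names Poisson regression without naming a variance estimator, so it excludes neither a scale parameter nor robust errors. That detail commonly sits in an analysis plan, which is not shown, and its absence is no finding. Nor does the text show that events recur or cluster within a person.

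Finally, no hypothesis, alpha or decision rule is attached to this comparison. It is a supporting safety summary.

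**Conclusion.** The concern holds as a risk. The capture rule and the comparison rule, taken together, allow recorded rates of common events to depend on assignment, and the effect would be to inflate the active-arm rates relative to control. It applies to the two active-versus-control contrasts and not to Small versus Large Changes. The primary weight analysis is untouched.

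The size cannot be taken from the documents. Under the assumed capture shares, a null rate ratio would read 1.02 to 1.06 if the assessments catch 90% of events, 1.05 to 1.13 at 80%, 1.19 to 1.50 at 50%, and 1.00 if they catch everything.

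The variance point is conditional: Poisson errors would be too small if events are overdispersed, and correct if they are not. It supports a precaution, not a criticism. Overall this is a worthwhile, low-cost improvement to a supporting analysis.

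**What to change.** - State whether intervention sessions count as in-person visits for event collection.
- Flag the source of each event record: common assessment, other contact, or both. Assessors should ask in full whatever has already been logged, so that an event reported earlier by contact can still count as elicited at the assessment.
- Base the between-arm Poisson comparison on events elicited at the common masked assessments, with person-time running to the last assessment attended.
- List contact-reported events separately by arm, and give an all-source comparison as a sensitivity analysis.
- Tally all serious events regardless of source.
- As a safeguard, use a robust variance or a negative binomial model with a person-time offset.

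**Cost.** A source field and a few sentences of analysis text; no new data collection. The comparison uses fewer events. It also omits contact-reported events from participants lost before their next assessment; planned losses are 7.5% at month 4 and 7.5% + 7.5% = 15% by month 12. The separate listing and the sensitivity analysis keep those events in view. Restricting the source does not correct any difference between arms in recall or in attendance at the assessments themselves.
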